### 2.15. Statistical Methods

The analyses of this study will follow the intention-to-treat (ITT) principles. All statistical analyses will be performed with SPSS v.22.0 software (SPSS Inc., Chicago, IL, USA), considering a level of *p* < 0.05 as statistically significant. Normality of distributions will be assessed using the Shapiro–Wilk test. A descriptive analysis of the variables will be carried out with punctual estimation and a confidence interval for 95% of security, treating the continuous variables as means, standard deviation, or medians according to the distribution of the variable. Categorical variables will be presented in frequencies and percentages. Continuous variables will be compared by Student’s “t” test and by analysis of variance (ANOVA), depending on the existence of 2 or more groups in each comparison. The association between categorical variables will be analyzed using the chi-square test. Studies of correlations between the variables will be carried out using the Pearson or Spearman test based on the normality of the analyzed variables.

Per protocol analysis will be performed within participants that fulfill the intervention. This approach will be used only for the primary outcomes and will be treated as a secondary analysis. In the case of a relevant number of missing values, multiple imputation or pattern mixture models will be used.

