## 2. Methods

### 2.1. Study Objectives

The objective of this study is to evaluate whether a pre-surgical nutritional intervention based on a high-fiber diet rich in PUFAs can revert gut microbiota alterations, surgical site infections, and anastomotic leaks in patients with CRC undergoing elective surgery (colonic resection with anastomosis), compared to a control group following standard nutrition recommendations.

To achieve this objective, three major aims are defined:To determine the change in the gut and intra-tumoral microbiome composition, fecal and serum levels of short-chain fatty acids (SCFAs), and serum inflammation, endotoxemia, and intestinal permeability markers in CRC patients following a high-fiber diet rich in PUFAs in the preoperative phase, in comparison to the control group.To evaluate the rate of anastomotic dehiscence and surgical site infections after surgery (30 days of follow-up) in the intervention group, in comparison to the control group.To establish the length of hospitalization, recurrences of CRC, response to adjuvant therapy, and overall and disease-free survival after surgery (1 year of follow-up) in the intervention group, in comparison to the control group.

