### 2.13. Data and Sample Collection and Analysis of Variables

#### 2.13.1. Data Collection

Data and samples will be obtained at 3 different time points: at baseline, the day before CRC surgery, and one year after surgery. For data collection, a complete clinical evaluation of the patients will be performed, which will include the registration of anthropometric data (height, weight, body mass index (BMI), waist-to-hip ratio, blood pressure), information about the patient’s medication, and assessment of dietary intake using validated food frequency questionnaires (FFQs) [21]. Baseline dietary fiber and PUFA intake will be estimated from the FFQs. All participants will be asked to complete a food diary during the 4 weeks of intervention for assessment of dietary changes.

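### Continuous outcomes are compared by t-test or ANOVA with no baseline covariate and no role for the normality test: valid but inefficient, and the test for individual taxa is left unclear

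*Protocol article*

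**What the plan says.** Section 2.1 sets the first aim as a change: "To determine the change in the gut and intra-tumoral microbiome composition, fecal and serum levels of short-chain fatty acids (SCFAs", followed by markers of inflammation, endotoxemia and permeability. Section 2.9 likewise words the microbiota part of the primary outcome, and the SCFA secondary outcome, as changes. Section 2.13.1 supplies the measurements: "Data and samples will be obtained at 3 different time points: at baseline, the day before CRC surgery, and one year after surgery".

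Section 2.15 fixes the comparison: "Continuous variables will be compared by Student’s “t” test and by analysis of variance (ANOVA", with the choice between the two "depending on the existence of 2 or more groups in each comparison". It adds "Normality of distributions will be assessed using the Shapiro–Wilk test". The distribution then decides between means and medians in the descriptive tables, and for correlations the "Pearson or Spearman test based on the normality of the analyzed variables". No such branch is given for comparing the arms. The threshold is set by "considering a level of *p* < 0.05 as statistically significant", and the software by "All statistical analyses will be performed with SPSS v.22.0 software".

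Section 2.13.3, by contrast, assigns microbiota composition, diversity and richness to QIIME2, and functionality to PICRUST.

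**The concern.** Three features of the stated rule fit these data poorly.

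- **Baseline.** Each patient's own starting value is available for stool, blood and tumour measures, yet the named tests include no covariate. The sample size (2.11) rests on anastomotic leak alone, so the mechanistic outcomes have no precision planned for them.
- **Shape.** Cytokines, LPS, zonulin, SCFAs and length of stay are likely to be right-skewed. A normality test is run, but a variable that fails it would be summarised by its median and still compared by a t-test on means.
- **Taxa.** Microbiota composition is part of the primary outcome and no taxon or index is singled out. If the single 0.05 threshold is applied taxon by taxon, some taxa may be reported as changed even if the diet does nothing.

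**Working it through.** **Plan's own figure.** The article gives no power or sample size for any continuous or microbiota outcome, so there is none to reproduce here. The check takes 48 analysable patients per arm from section 2.11 (recruited: 48/0.9 = 53.3, so 54).

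**Assumed inputs, because the article does not give them.** Baseline/pre-surgery correlation r = 0.3 to 0.7; equal variance at both times; true difference 0.5 SD; two-sided 0.05; 10 to 100 taxa.

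**1. Baseline adjustment.** Take the variance of one measurement as 1. The variance is 2(1−r) for a change score, 1 for the pre-surgery (post) value and 1−r² for ANCOVA. ANCOVA relative to change score is therefore (1−r²)/[2(1−r)] = (1+r)/2, and relative to the post value 1−r². Neither ratio exceeds 1. Power is Φ(0.5·√(48/2)/s − 1.96), where s is the square root of the variance.

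| r | Change score: variance, power | Post value: variance, power | ANCOVA: variance, power | ANCOVA/change | ANCOVA/post |
|---|---|---|---|---|---|
| 0.3 | 1.40, 54% | 1, 69% | 0.91, 73% | 0.65 | 0.91 |
| 0.5 | 1.00, 69% | 1, 69% | 0.75, 81% | 0.75 | 0.75 |
| 0.7 | 0.60, 89% | 1, 69% | 0.51, 93% | 0.85 | 0.51 |

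At r = 0.5, ANCOVA with 48 per arm matches a post-value t-test with 48/0.75 = 64 per arm. Below r = 0.5 the change score is less precise than the post value alone.

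**2. Skew.** Log-normal data were simulated with 48 per arm, 10,000 trials per setting and a true shift of 0.58 SD on the log scale.

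| Log SD | Type I error, raw t | Power, raw t | Power, t on logs | Power, Mann–Whitney |
|---|---|---|---|---|
| 1 | 4.2% | 62% | 81% | 79% |
| 1.5 | 3.4% | 44% | 80% | 79% |
| 2 | 2.5% | 30% | 80% | 78% |

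The raw test is conservative under no effect and loses 19 to 50 percentage points of power against the log-scale test.

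**3. Taxa tested singly at 0.05 with no effect.** The expected number of false positives is 0.05m. For independent taxa, P(at least one) = 1 − 0.95^m.

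| Taxa m | Expected false positives | P(at least one), independent | P(at least one), correlation 0.5 (simulated) |
|---|---|---|---|
| 10 | 0.5 | 40% | not run |
| 20 | 1 | 64% | 42% |
| 50 | 2.5 | 92% | 62% |
| 100 | 5 | 99.4% | 78% |

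**4. Relative abundances.** Proportions sum to one, so a rise in one taxon pushes the others down. With 30 simulated taxa, of which one common taxon truly rose 4-fold, the t-test on relative abundance rejected a truly unchanged taxon 19% of the time, against 4.7% when nothing changed.

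**The case against.** The strongest reply is that the stated comparison is not wrong. Because the outcomes are worded as changes, the t-test can be read as a test of change scores, which uses the baseline and is valid in a randomised trial. In some settings ANCOVA adds little: 69% to 73% power against the post value at r = 0.3, or 89% to 93% against the change score at r = 0.7. The article gives no correlation from which to choose. This stands, and it makes baseline adjustment a gain in efficiency and not the correction of an error.

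Three stronger readings are tempting, and the documents do not support them.

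- *The plan ignores baseline.* It does not adjust for baseline, but sections 2.1 and 2.9 define outcomes as changes.
- *Skew produces false positives.* In the simulations type I error stayed below 5%; the cost is power.
- *False-positive taxa are guaranteed.* No number of taxa is given, and section 2.13.3 may place the composition analysis in QIIME2, outside the t-test rule.

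It is also fair to say that FDR control, log-ratio methods and zero handling are details an article commonly leaves to a fuller document. Their absence alone is therefore not the point. What remains is text that is stated: a t-test or ANOVA as the only comparison, a normality test with no effect on it, one 0.05 threshold, and two sections that disagree on where microbiota data are analysed.

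**Conclusion.** The point holds as a matter of efficiency and clarity. The arm comparison in section 2.15 is valid, but it is less precise than one that uses the collected baseline as a covariate. Variance under ANCOVA would be 65–85% of the change-score analysis and 91–51% of the post-value analysis, if r lies between 0.3 and 0.7. For markedly skewed markers the raw t-test costs power, to an extent that depends on the assumed log-normal spread, and its error rate is not inflated. The Shapiro–Wilk step has no consequence where it matters most.

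For taxa the conclusion is conditional. Sections 2.13.3 and 2.15 do not agree on how they are analysed. If the 0.05 rule applies to each, at least one false positive is likely once there are about 20 or more independent taxa; correlation between taxa lowers that chance but leaves the expected number unchanged. The compositional effect in step 4 depends on the simulated scenario and shows the direction of the problem only.

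**What to change.** Revise section 2.15 as follows, before any results by arm are seen, since the trial is open-label.

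- **Biological markers.** Compare the pre-surgery value between arms by ANCOVA with arm and the patient's own baseline value as terms, on the log scale for SCFAs, cytokines, LPS and zonulin.
- **Length of stay.** Use a rank test or a log-scale comparison.
- **Normality testing.** Choose the scale in advance, as above, so that Shapiro–Wilk is not needed to decide the comparison.
- **Microbiota.** Reconcile sections 2.13.3 and 2.15 by saying which analyses run in QIIME2 and which in SPSS, and at what threshold. Use one global between-arm community test, stating how the baseline sample enters it. Then analyse taxa by a compositional method with a stated rule for zeros and FDR control. PERMANOVA, centred log-ratios and Benjamini–Hochberg at 5% would serve; other methods of the same kind are acceptable if named in advance.

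The cost is a paragraph of text and a little more analysis work. No new data, samples or patients are needed.

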## Abstract

Colorectal cancer (CRC) is the third most common cancer and the second cause of cancer death worldwide. Several factors have been postulated to be involved in CRC pathophysiology, including heritable and environmental factors, which are the latest to be closely associated with nutritional habits, physical activity, obesity, and the gut microbiota. The latter may also play a key role in CRC prognosis and derived complications in patients undergoing surgery. This is a single-center, open, controlled, randomized clinical trial, in patients with scheduled surgical intervention for CRC. The primary objective is to assess whether a pre-surgical nutritional intervention, based on a high-fiber diet rich in polyunsaturated fatty acids (PUFAs), can reduce disturbances of the gut microbiota composition and, consequently, the rate of post-surgical complications in patients with CRC. Patients will be randomized in a 1:1 ratio after receiving a diagnosis of CRC. In the control arm, patients will receive standard nutritional recommendations, while patients in the intervention arm will be advised to follow a high-fiber diet rich in PUFAs before surgery. Participants will be followed up for one year to evaluate the overall rate of postsurgical complications, recurrences of CRC, response to adjuvant therapy, and overall/disease-free survival.

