### 2.9. Outcomes

The primary outcome includes the evaluation of changes in the gut and intra-tumoral microbiota composition and its relationship with the postoperative rate of anastomotic leakage and surgical site infection after the nutritional intervention. Secondary outcomes will include the determination of changes in SCFA levels in serum and feces, serum levels of inflammation markers, endotoxemia, and intestinal permeability, length of hospitalization after surgery, recurrence of CRC after surgery, response to adjuvant therapy, and post-surgical survival rates.

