## 3. Discussion

To the best of our knowledge, this is the first study protocol evaluating the impact of a pre-surgical nutritional intervention based on high-fiber intake with high levels of PUFAs on altered gut microbiota and its relationship with post-surgical complications, especially anastomotic leaks and site infections. Previous studies on human subjects have demonstrated the modulation of the microbiota through dietary interventions, even in the short term [23,24,25]. In this direction, the consumption of diets rich in PUFAs have been shown to modulate the gut microbiota composition, favoring the growth of protective bacteria such as *Bifidobacteria* and *Lactobacilli*, while reducing the presence of pathobionts such as *Porphyromonas* spp. after 6 weeks of treatment [20,26,27]. Thus, our hypothesis is that the intake of a fiber-rich diet with high levels of PUFAs prior to CRC surgery could lead to a modified, more balanced gut microbiota, which could result in a lower number of complications after surgery.

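### Section 2.15 names only two-variable tests without randomised arm, so a microbiota–complication association pooled over arms could not support the causal reading

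*Protocol article*

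**What the plan says.** Section 2.9 defines the primary outcome as "changes in the gut and intra-tumoral microbiota composition and its relationship with the postoperative rate of anastomotic leakage and surgical site infection". The relationship is therefore part of the primary outcome, not an exploratory extra.

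Two other places give it a causal direction. The Abstract's primary objective is to assess whether the diet "can reduce disturbances of the gut microbiota composition and, consequently, the rate of post-surgical complications in patients with CRC". The hypothesis in section 3 is that the diet "could lead to a modified, more balanced gut microbiota, which could result in a lower number of complications after surgery".

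Section 2.15 lists the methods:
- Continuous variables are compared by Student's t test "and by analysis of variance (ANOVA), depending on the existence of 2 or more groups in each comparison".
- For categorical variables: "The association between categorical variables will be analyzed using the chi-square test".
- For correlations: "Studies of correlations between the variables will be carried out using the Pearson or Spearman test based on the normality of the analyzed variables".

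Each method relates two variables. No regression, stratified, within-arm or mediation analysis is named. The section does not say which method serves the relationship in section 2.9, or whether it is run over both arms together.

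**The concern.** The hypothesis has the diet acting on two things, the microbiota and the complication rate. If it does both, randomised arm is a common cause of the two. Diet-arm patients then tend to have the shifted microbiota and fewer leaks. A test over all patients finds an association even if, within each arm, a patient's microbiota change says nothing about that patient's risk of leak. This would happen if the fall in leaks came by another route, for example general nutritional status.

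A significant pooled result could then restate that the arms differ on two variables while appearing to support the causal chain. The better the diet works on both, the more often this happens. At stake is the mechanistic part of the primary outcome. The randomised comparisons of microbiota and of complications between arms are not affected.

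**Working it through.** **Inputs from section 2.11.** Leak 30% (control) and 10% (diet), significance level 5%, power 0.8, 48 evaluable per group, 54 recruited.

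**The plan's own figure.** With the pooled-variance formula and a one-sided 5% level, n = (1.645·√(2·0.2·0.8) + 0.842·√(0.21 + 0.09))² / 0.2² = 48.4 per group, so 48 is reproduced to within rounding. A two-sided level gives 62. Losses: 48/0.9 = 53.3, rounded up to 54, which agrees. Sidedness is a separate matter; 48 per group is used here as the plan's evaluable number.

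**Assumption.** The protocol gives no size for the diet's effect on microbiota. Let the microbiota measure be a single normal score with SD 1 within arm, shifted by d in the diet arm, and take d from 0 to 2. Leak depends on arm only, so the within-arm link is zero.

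**Induced correlation.** With 1:1 allocation the arm indicator has variance 0.25. The pooled leak rate is 20%, with variance 0.16. Then

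|r| = d·0.25·0.20 / √((1 + d²/4)·0.16)

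For d = 1 this is 0.05/√(1.25·0.16) = 0.112. With 96 patients the expected test statistic is about 0.112·√96 = 1.10, and P(Z > 1.96 − 1.10) is about 0.19.

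**Simulation.** Two-sided 5% tests, 48 per arm. The pooled column gives the range over Pearson, Spearman and t test in separate runs.

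| Shift d (SD) | Induced r (absolute) | Pooled test rejects |
|---|---|---|
| 0 | 0 | about 5% |
| 0.3 | 0.037 | about 6% |
| 0.5 | 0.061 | 8–9% |
| 0.8 | 0.093 | about 14% |
| 1.0 | 0.112 | 17–20% |
| 1.5 | 0.150 | 30–33% |
| 2.0 | 0.177 | 41–45% |

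**Sensitivity.**
- 54 per arm: about 10% at 0.5 SD and 20–22% at 1 SD.
- Leak 15% versus 5%: about 7%, 11% and 16% at 0.5, 1 and 1.5 SD.
- Equal leak of 20% in both arms: about 5% at 0.5, 1 and 1.5 SD.

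**With arm in the model.** A linear arm-adjusted test rejects in 4.5–5.9% of runs over the same shifts. Firth logistic regression with change, arm and baseline rejects in 4.4–5.2%. Expected leaks are 48·0.30 + 48·0.10 = 19.2.

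**What adjustment does not do.** With no diet effect on either variable, leak 30% in both arms and a shared latent cause (loading 0.4 on each), the unadjusted and arm-adjusted tests both reject in about 21% of runs.

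**Price in precision.** Adding arm multiplies the variance of the microbiota coefficient by about 1 + d²/4 (linear approximation). The standard error rises by √1.25 = 1.12 at 1 SD and √2 = 1.41 at 2 SD.

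**The case against.** The strongest reply is that pooling is not written down. The correlation sentence in section 2.15 names neither microbiota, leak, infection nor arm, and it is compatible with correlations computed within each arm. Offering ANOVA for more than two groups in a two-arm trial also suggests groupings other than arm. This stands: a reader might infer that the plan commits to a pooled correlation, but the text does not say so, and the point has to be conditional.

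A second reply is that this is detail an article leaves to the full protocol or analysis plan. It stands only in part. Covariate lists may be left out, but section 2.15 does state which kinds of test relate variables, and none of them includes arm.

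A third reply is that section 2.9 speaks of a relationship, which is an association, while the Abstract and Discussion state an objective and a hypothesis, the latter in cautious terms. The numbered aims in section 2.1 compare intervention with control, and none of them is the correlation. This stands too. Nowhere is it written that a significant correlation will be taken as proof of mechanism.

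Finally, the size depends on an assumed shift, on a single normal score where section 2.13.3 plans composition, diversity and richness analyses in QIIME2, and on the whole fall in leaks coming by another route. That limits the magnitude but not the direction.

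**Conclusion.** The point holds in conditional form and should be addressed. The named tests cannot separate a microbiota–complication link from the effect of arm on both variables. The excess is modest at a shift of 0.5 SD or less and exceeds twice the nominal level from about 0.8 SD, at the plan's own leak rates. It is smaller at lower leak rates and disappears if the diet fails to move either variable. The assumptions are pooled arms, no within-arm link, and a shift size that the protocol does not give.

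A reader might infer that the plan has a type I error of up to 45%. The documents do not support that. A pooled test is valid for the marginal association, which is real in these scenarios, and the documents state no null of no association beyond arm. The error would lie in taking a rejection as support for the causal step in the Abstract and Discussion.

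**What to change.** In section 2.15, name the analysis for the relationship part of the primary outcome: a Firth-penalised logistic regression of leak, and separately of surgical site infection, on the change in the chosen microbiota measure from baseline to before surgery, with randomised arm and the baseline microbiota value as terms. Report the estimate with its 95% confidence interval.

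In section 2.9, state that this is an association adjusted for arm and does not establish mediation, because microbiota change is not randomised and common causes of dysbiosis and complications within arm remain.

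No new patients, visits or samples are needed: section 2.13 already provides stool at baseline and the day before surgery, and tumour tissue at colonoscopy and surgery. The cost is precision. With about 19 expected leaks and three model terms the interval widens, by roughly 12% in standard error at a 1-SD shift and about 40% at 2 SD, and the mechanistic claim becomes more modest.

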## 3. Discussion

To the best of our knowledge, this is the first study protocol evaluating the impact of a pre-surgical nutritional intervention based on high-fiber intake with high levels of PUFAs on altered gut microbiota and its relationship with post-surgical complications, especially anastomotic leaks and site infections. Previous studies on human subjects have demonstrated the modulation of the microbiota through dietary interventions, even in the short term [23,24,25]. In this direction, the consumption of diets rich in PUFAs have been shown to modulate the gut microbiota composition, favoring the growth of protective bacteria such as *Bifidobacteria* and *Lactobacilli*, while reducing the presence of pathobionts such as *Porphyromonas* spp. after 6 weeks of treatment [20,26,27]. Thus, our hypothesis is that the intake of a fiber-rich diet with high levels of PUFAs prior to CRC surgery could lead to a modified, more balanced gut microbiota, which could result in a lower number of complications after surgery.

